#### Research question 2: does using the IBH-PC toolkit affect the degree of practice-level behavioral health care integration in primary care practices?

We will use GLM models of practice integration level (total PIP and PIP domains) to perform intention-to-treat analyses as a function of experimental condition (active vs. control) and practice characteristics. The parameters of interest are the central tendency (median), statistical significance (P values) and 95% CI of the change in total PIP and PIP domains from baseline to follow-up.

Practice characteristics will be measured at baseline and will include ownership type, specialty, training status, non-profit status, size, region, census-tract based variables, primary care medical home (PCMH) status, and % Medicare patients.

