## Methods: Participants, interventions, and outcomes

### Study setting {9}

The IBH-PC study takes place in 45 primary care practices across the United States (Fig. 1). Practices represent a diverse distribution of geographic regions, population densities (urban vs. rural), patient population size, specialty (family vs. internal medicine), community health centers, federally qualified health centers, nonprofit and for-profit organizations, resident training sites, and ownership (hospital or health system, academic, private).

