### Eligibility criteria {10}

#### Study practices

Primary care practices are eligible to participate if they:
Have at least one PCP and at least one BHP onsite (co-located),Have at least 0.5 full-time equivalent BHPs licensed to practice independently,Commit to maintaining onsite BHP for the duration of the study,Provide the research team with access to electronic medical records (EMRs) to identify patients with specific medical and behavioral health conditions for recruitment,Are willing to complete survey instruments periodically throughout the study, andAre willing to be randomized to either the active or control arm.

For practices with more than 10% of their revenue generated by Medicare, at least one BHP per practice must be eligible to bill Medicare. Practices are ineligible if they are already undergoing, or plan to undergo, another QI initiative similar to the IBH-PC intervention or if they already have an advanced level of BH integration as evidenced by a total Practice Integration Profile score (PIP) above 75. The PIP is a survey of 30 items completed by primary care providers and staff about their own practice used to measure practice level integration [26, 27].

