## Trial status

The IBH-PC study information is available on ClinicalTrials.gov, protocol version 4, April 16, 2019. Practice recruitment began when the study was funded on April 1, 2016. Currently, 45 primary care practices have been recruited for study participation. Two of these practices are participating as “Vanguard” (pilot) sites and are not contributing data to the main analyses. One practice withdrew from the study, leaving 42 participating practices. Twenty of these practices are randomized to the active arm and 22 to the control arm.

Patient participant recruitment began in September 2017. Currently, there are 3006 patient participants who have completed baseline surveys and may be eligible for the main analyses if they complete follow-up surveys. Follow-up data collection concluded in December 2020. Data processing is underway.

Eight IBH-PC active practices have been recruited for inclusion in the qualitative case study analysis focused on examining factors associated with supporting or impeding behavioral health integration and data collection is complete. For the cost assessment analysis, 8 IBH-PC active practices were been recruited and data collection is complete. Recruitment and data collection were completed in December 2020.

Due to the complex nature of the study intervention and potential need to respond with modifications, the study team chose to submit the protocol for publication near the conclusion of the follow-up data collection period in order to ensure accuracy in the reported details.

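### The PIP model for research question 2 does not list pre-randomization PIP as a covariate, leaves open which PIP is the baseline, and calls its effect a median

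*Protocol article*

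**What the plan says.** All references are to the protocol article.

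- **Model.** Under Statistical methods, Research question 2, total PIP and its domains are analysed by GLM (generalized linear mixed, per the abbreviations list) on arm and practice characteristics. The list reads "Practice characteristics will be measured at baseline and will include ownership type, specialty, training status, non-profit status, size, region, census-tract based variables". Medical-home status and percent Medicare complete it, making nine named items.
- **Parameter.** "The parameters of interest are the central tendency (median), statistical significance (P values) and 95% CI" of the change from baseline to follow-up. For the PROMIS-29 outcomes, the same model class is paired with a mean.
- **Sample.** Trial status, after setting aside the two Vanguard sites: "One practice withdrew from the study, leaving 42 participating practices". On the split between arms it adds: "Twenty of these practices are randomized to the active arm and 22 to the control arm".
- **PIP before allocation.** Study practices {10} excludes practices with an "advanced level of BH integration as evidenced by a total Practice Integration Profile score (PIP) above 75". Sequence generation {16a} stratifies on baseline total PIP (below, or at or above, the 50th percentile) and on geographical area. Under Implementation {16c} the stratum is determined before the envelope is opened.
- **Timing.** Plans for assessment and collection of outcomes {18a} puts the baseline period at 0 to 12 months after randomization.
- **Use of medians.** Outcomes {12} lists change in median PIP. Recruitment {15} measures a practice's change, for case-study selection, as the difference between its median PIP scores at two waves.

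**The concern.** Research question 2 asks whether the toolkit changes integration, the route by which it is meant to help patients. A null or positive patient result is hard to read without a clear PIP estimate. Three things weaken that estimate as written.

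1. The covariate list has region, which corresponds to one stratification factor, but not PIP, which is the other factor and the outcome's own earlier value.
2. The word baseline has two possible referents: the score used for stratification, which precedes allocation, and the outcome wave, which follows it. Practices know their arm once randomized, so a baseline taken months into an active practice's work could already contain part of the effect.
3. The named parameter does not match what the model estimates.

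**Working it through.** The article states no power, standard error or precision for PIP, so there is no figure to reproduce.

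**Practice count.** 45 recruited − 2 Vanguard − 1 withdrawn = 42 = 20 + 22.

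**Change score against baseline adjustment.** Let σ² be the between-practice variance of PIP, taken as equal at both times, and ρ the baseline/follow-up correlation. The article gives neither; ρ from 0.3 to 0.9 is assumed.

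- Change score: variance 2σ²(1 − ρ).
- Follow-up adjusted for baseline: variance σ²(1 − ρ²).
- Ratio: 2(1 − ρ)/(1 − ρ²) = 2/(1 + ρ).

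| ρ (assumed) | Variance ratio | Interval ratio (square root) |
|---|---|---|
| 0.3 | 2/1.3 = 1.54 | 1.24 |
| 0.5 | 2/1.5 = 1.33 | 1.15 |
| 0.7 | 2/1.7 = 1.18 | 1.08 |
| 0.9 | 2/1.9 = 1.05 | 1.03 |

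The added covariate costs one degree of freedom. With 42 practices the variance factor is 39/38 = 1.026, and the interval is about 1.4% wider with the change in the t quantile. That leaves a small net gain even at ρ = 0.9 (1.026/1.014 = 1.012).

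**Which baseline.** Let Δ be the true arm difference at follow-up, and δ the arm difference already present at a post-randomization baseline wave. A change score from that wave estimates Δ − δ. Follow-up PIP adjusted for a pre-randomization value estimates Δ. The article gives no δ, so the loss cannot be sized. It is zero if the change starts from the stratification score.

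**Length of the covariate list.** Take one row per practice and p covariate parameters that are unrelated to arm and explain nothing. The variance factor is (42 − 3)/(42 − 3 − p). The interval factor is its square root times t(0.975, 40 − p)/t(0.975, 40). The covariates pay for themselves once they explain R² = 1 − 1/(interval factor)².

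- p = 9, one parameter per named item: 39/30 = 1.30, 31 residual df, interval factor 1.15, break-even R² 0.25.
- p = 12, assumed coding: 39/27 = 1.44, interval factor 1.22, break-even 0.33.
- p = 19, assumed coding: 39/20 = 1.95, interval factor 1.44, break-even 0.52.

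Nine is a floor: the census-tract item is plural, and Study setting {9} gives "ownership (hospital or health system, academic, private", three categories. The true p is not stated.

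**Median.** If the response is each practice's median over its respondents, the arm coefficient is a mean difference in practice medians. If the target is the median change across practices, this model class does not estimate it. The research question 2 text fits neither reading as worded.

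**The case against.** **Baseline PIP is already in the analysis.** The outcome is a change, so a baseline value enters as the subtracted score, or as the first repeated measure. This is right, and a reader should not infer that the plan ignores baseline PIP. It does not supply the adjustment, though: with complete data, an unconstrained arm-by-time contrast from baseline to follow-up has the same variance as the change score.

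**The baseline may be the pre-randomization score.** Sequence generation calls the stratifying score the baseline degree of integration, and the 0 to 12 month window covers outcome collection generally. This stands as an ambiguity. A reader might infer that the effect is biased by a post-randomization baseline; the document shows only that it could be.

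**The list may be incomplete.** It is introduced as what the characteristics will include, and an analysis plan that is not shown may add PIP or settle coding. That is fair and limits the criticism. Still, the article goes so far as to name nine items, including a counterpart to one stratification factor and not the other.

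**Precision.** It is tempting to conclude that nine or more covariates on 42 practices will make the estimate imprecise. The article does not support that. No covariate R² or PIP standard deviation is given, and ownership, specialty and medical-home status could be prognostic. The section on missing data {20c} describes models with time as an explicit covariate. Under that reading the effect is arm-by-time, and practice traits entered as main effects cost it little.

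**The median is a within-practice summary.** Outcomes and Recruitment point that way, and the analysis is then coherent. The label remains wrong, because the model's effect is a mean difference in those medians.

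**Conclusion.** The point holds for a secondary outcome. The PIP model as described does not list the pre-randomization PIP that the trial must already hold. Relying on an unadjusted change score instead costs 24% to 3% in interval width for ρ from 0.3 to 0.9. This rests on equal variances at the two times and on a pre-randomization score that predicts follow-up as well as the change-score baseline would. The choice of baseline is unsettled, with possible but unquantified attenuation if the later wave is used. The median label is a small, real mismatch.

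Not established are that the PIP estimate will be imprecise because of the covariate count, that baseline PIP is absent altogether, or that the effect is in fact biased. The covariate count is a possible risk: about 15% in interval width at nine parameters in a one-row-per-practice model with uninformative covariates, gone once they explain about a quarter of the variance.

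**What to change.** 1. Add continuous pre-randomization total PIP (the eligibility and stratification value) and the geographical stratum as covariates in the PIP model.
2. State that this value is the baseline for PIP, with follow-up PIP, or change from that same value, as the response; the two give the same arm effect once it is a covariate. Adding the covariate while still subtracting a later wave would not remove the attenuation described above.
3. Replace the median wording with an adjusted mean difference in practice-level median PIP. If a median effect is intended, name quantile regression.
4. Optional: keep the remaining practice characteristics for a sensitivity analysis. This is a trade-off. It saves degrees of freedom but gives up adjustment for chance imbalance, and loses precision if those traits are prognostic.

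The cost is analysis wording and one or a few degrees of freedom. No new data are needed. Trial status reports that data processing is under way, so the change should be made and dated before arm comparisons are run.

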#### Research question 3: what factors support or impede successful integration of behavioral health care into primary care practices?

A cross-case comparative analysis [53, 61, 62] will be conducted for selected case study practices. Practices will be selected from the extremes of change in the main outcome variable, and additional practices maybe selected for confirming/disconfirming analyses [66]. Data collected from the individual case study sites will be analyzed to identify site-specific contextual factors that support or impede integration. Through multiple rounds of coding the data, researchers will organize and categorize related evidence on a topic from multiple data sources, assisting with pattern identification in preparation for thematic analysis [62, 67].

After analysis at the individual practice level, a cross-case study analysis will be conducted to identify prominent themes. This process allows for the in-depth examination of the individual practice sites to be followed by a cross-cutting analysis of integration processes. Findings will include themes and insights regarding the factors that supported or impeded successful integration of behavioral health care across the selected practices.

#### Research question 4: what are the costs of implementing the IBH-PC toolkit?

Descriptive statistical and basic econometrical (i.e., time/effort-cost estimation) methods will be used to summarize findings. Costs of IBH-PC toolkit implementation will be measured only, while research costs (identifying eligible patients, collecting and analyzing research data, etc.) and changes in operational costs and revenues *after* completion of the intervention will not be included.

### Interim analyses {21b}

Not applicable. Interim analyses and stopping guidelines are not planned for this study due to the low risk nature of the practice-level intervention.

### Methods for additional analyses (e.g., subgroup analyses) {20b}

#### Subgroup analyses

Subgroup analyses will be conducted to understand if the IBH-PC toolkit is more or less effective for various patient and practice groups. Specific patient subgroups to be tested include gender, age in quartiles, race (white vs. other), education (less than high school graduation, high school diploma, college degree), degree of multi-morbidity (2 vs. > 2 qualifying conditions), and each of the qualifying conditions.

Specific practice subgroups will be analyzed based on practice size, staffing, geography, and financial structure.

These subgroup analyses will follow the same plan as the primary analysis except that an additional characteristic (representing subgroup membership) will be included as well as its interaction with the experimental condition.

### Exploratory analyses

We will replace the binary predictor variable (active vs. control) with continuous variables (the PIP total score and its subscales) to answer the question: What is the relationship between a practice’s degree of behavioral health care integration and patient-centered outcomes?

### Methods in analysis to handle protocol non-adherence and any statistical methods to handle missing data {20c}

We will employ the “intention-to-treat” principle; analyses will be conducted according to a practice’s randomization assignment. The final analysis population will be fully described and differences from the enrolled population will be presented. An advantage of GLM models with time of measurement as an explicit covariate is that equal numbers of data points and equally spaced intervals between data points are not required [68], so subjects without complete data still contribute to the analysis. Cases that are lost may remain in the analysis, although they will provide less information and reduce the variance of estimated effects less than cases that are present for all measurement times.

### Plans to give access to the full protocol, participant level-data and statistical code {31c}

The study is registered on ClinicalTrials.gov (NCT02868983). A complete, cleaned, de-identified copy of the final dataset used in conducting the final analyses will be made available within 1 year of study completion. It will include a data dictionary with response options and missing values defined as well as a complete set of survey instruments (excluding copyright-protected material not licensed for transfer). The data will be available as an Stata data set or comma-separated file. We will not make data from qualitative results available because of the potential for identifying individuals. Despite redacting interviewees’ names from their transcripts, there remains potential for identification by other information shared throughout the interviews. This is particularly relevant given our focus on contextual factors, which necessarily include information about the practice and surrounding community. We concluded that it would not be feasible to determine all of the potentially identifiable data that would need to be redacted to protect the identity of interviewees.

Outside investigators who wish to use the data may request them from the PI. They will be encouraged to collaborate with the research team as appropriate. If the research question they propose is not already under analysis by a member of the research team, the data will be encrypted and sent via SFTP or other secure transfer protocol. If outside investigators wish to reproduce any of our analyses, a full description of our methods (including statistical programming scripts in Stata) as well as consultation by the PI, statistical investigators or others as appropriate, will be made available.

Outside investigators will be required to follow all the protocols for confidentiality, security, notifications to the study sponsor (PCORI), acknowledgments of funding, etc. required of the research team.

### Oversight and monitoring

#### Composition of the coordinating center and trial steering committee {5d}

The research team includes expertise in behavioral and medical management, research design, multicenter data collection, epidemiology and biostatistics, patient engagement, practice transformation, continuing education, quantitative outcomes assessment, and qualitative analysis of processes and outcomes. The team also includes several patients and other stakeholders from the multiple chronic conditions community who provide expertise from lived experience.

#### Composition of the data monitoring committee, its role and reporting structure {21a}

The Data and Safety Monitoring Board (DSMB) is an independent group that advises the IBH-PC study investigators. The members of the DSMB serve in an individual capacity and provide their expertise and recommendations. They report to the PI.

The primary responsibilities of the DSMB are to (1) periodically review and evaluate reports of potential adverse events reported by study participants, personnel, or others; (2) determine the causality and severity of adverse events; and (3) make recommendations for changes in study protocols, operations, or consent procedures as a result of their findings. The DSMB considers study-specific data as well as relevant background knowledge of the patient population under study.

The chair of the DSMB is a patient. Additional members include a PCP, a Psychiatrist, and a BHP.

The DSMB meets at least annually and whenever the PI determines that a significant number of adverse events have been reported or a single adverse event report is potentially serious and warrants DSMB review.

### Adverse event reporting and harms {22}

Although the intervention is low risk, it is possible that a research participant could suffer an unanticipated or adverse event related to the study. If such a concern is raised by study staff, a participant, an investigator, clinician, or any other party, the event is reported to the Institutional Review Board (IRB) and reviewed by the DSMB.

The DSMB determines the causality of each adverse event as “unrelated,” “related,” or “possibly related” to the IBH-PC toolkit or other aspects of the study. It determines the severity of each adverse event according to the Common Terminology Criteria for Adverse Events [69] (CTCAE). Recommendations for changes in the consent process or study protocol may be made, based on the nature of the adverse event.

### Frequency and plans for auditing trial conduct {23}

There are no plans for auditing trial conduct.

### Plans for communicating important protocol amendments to relevant parties (e.g., trial participants, ethical committees) {25}

Changes to the study protocol are communicated to all research team members electronically and reviewed in accordance with IRB policies. Through regular meetings with the study sponsor (PCORI), changes are discussed and tracked through a regular milestone reporting process.

### Dissemination plans {31a}

Dissemination is a standing agenda item for the Investigators and the Stakeholder Advisory Group (SAG). Research team and SAG members, as well as clinicians and patients at the clinical sites, may be asked to make presentations to health care providers, accountable care organizations (ACO), primary care organizations, health-related agencies, legislative committees, and business forums (employer and payer organizations) in their communities. Patient advisors will be asked to review all materials so that findings are understandable and usable by a broad audience. It is anticipated that study findings will be reported in numerous formats such as peer-reviewed literature, conference proceedings, blog posts, and policy briefs.

## Discussion

As IBH gains momentum and primary care practices are encouraged to provide integrated behavioral health services, evidence-based interventions that are shown to effectively increase practice integration levels will be important. This study evaluates the effectiveness of an evidence-based practice change intervention to improve patient outcomes in a vulnerable population and to increase a practice’s degree of integration. There are a number of strengths to our design. First, we are able to overcome a major obstacle in the study of integrated versus co-located practices by randomizing all practices and using co-location as the control condition. Second, we will be able to understand the impact of the IBH-PC toolkit on multiple domains of health and practice integration. Third, our patient recruiting procedure uses a trusted third party to consent patients so practices can remain blind to their patients’ participation status -- an important feature that reduces biases as practices apply newly-learned care approaches with their patients. Finally, the pragmatic nature of the intervention is a strength, as it provides flexibility in how the IBH-PC toolkit is used and which components of integration a practice chooses to apply at any given time.

The pragmatic study design is also a limitation in that it will be difficult to ascertain which aspects of the intervention are associated with any potential improved outcomes. However, supporting flexibility in how and when practices engage with the intervention is important for practice retention, and we will be able to examine which components of the IBH-PC toolkit are most vs. least commonly used by individual practices. Another study limitation is that, due to the complexity of longitudinal EMR extraction across multiple sites, we will not evaluate the impact of the intervention on physiologic outcomes such as blood pressure and hemoglobin A1C.

The study will provide both clinical trial and contextual information that is vital to efforts to improve the integration of behavioral and primary medical care [70, 71].

